### **7.2.4 How to report?**

The initial notification is reported in writing and in detail using the "Initial Serious Adverse Event Report" form (located in the appendix of the CRF).

The initial notification must contain, at a minimum, all of the following:

- an identifiable participant code
- an identifiable notifier
- the treatment of the test (FLYP(+)/ normal saline)
- ⊖ the adverse event (date of occurrence, intensity, relationship to the research)

Initial notification is followed by detailed written follow-up reports using the “Serious Adverse Event Follow-up Report” form (located in the appendix of the CRF.) to monitor the case’s progress or complete the information.

The investigator completes and sends the dated and signed SAE. report form, as well as any relevant anonymized document related to the SAE (e.g., laboratory results, examination or hospitalization reports...) to :

- **Regarding Hemovigilance:**

- These events must be declared without delay:

- **to the CTSA**

- **Concerning pharmacovigilance**

It does not concern FLYP, which is a labile blood product. However, for the proper conduct of the study, pharmacovigilance is set up for any product that does not directly concern FLYP.

- **to**

In the case of in utero exposure, the investigator completes the “Follow-up form for a pregnancy discovered during biomedical research” and faxes it to Hemovigilance.

The investigator must follow the pregnant woman until the end of the pregnancy or its termination and notify the sponsor of the outcome with this form. If the outcome of the pregnancy falls within the definition of serious adverse events (spontaneous abortion, t\_ermination of pregnancy, fetal death, congenital anomaly, etc.), the investigator must follow the procedure for reporting SAEs.

### **7.3 Sponsor’s responsibilities**

The sponsor is responsible for reporting to the ANSM and the CPP (Ethic Committee) any serious and unexpected adverse events attributable to the labile blood cell therapy product and/or the protocol within 15 days (7 days in the case of death and life-threatening events).

On the anniversary date of the first inclusion, the sponsor prepares a safety report including:

- the list of potential research drug product-related SAEs
- a concise and critical analysis of the safety of the participants involved in the research.

This report is sent to the ANSM and the CPP (Ethic Committee) within 60 days of the anniversary of the first inclusion.

### **7.4 Planned methods and timing for measuring, collecting, and analyzing safety assessment metrics**

#### **During the prehospital phase:**

A permanent presence of an emergency physician and a nurse with the person undergoing research. Continuous surveillance of the clinic, continuous monitoring of the constants: HR, BP, SpO2. Verification of the absence of signs of drug intolerance.

Collection of the different parameters in the prehospital CF.

The occurrence of adverse event(s) or the aggravation of adverse event(s) in the prehospital phase will be reported by the physician who managed the patient in the context of prehospital management.

#### **On admission to the hospital:**

Management by the emergency department or intensive care unit and implementation of departmental protocols for the management of patients in traumatic hemorrhagic shock; monitoring of the clinic and vitals (HR, BP, SpO2) Verification of the absence of signs of drug intolerance.

Collection of the different parameters in the hospital CRF.

The occurrence of an unexpected event or worsening of an unexpected event in the hospital phase will be reported by the department in charge of the patient.

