#### **Data collected at the hospital after admission:**

- Results of blood group prior to administration of FLYP
- Results of biological samples for hemostasis analysis before and after administration of FLYP: PT, APTT, fibrinogen, CRP, coagulation factors
- Results of arterial blood gas: lactate, PaO2 (FiO2 noted), if performed
- Clinical parameters at intake (HR, BP, RR, SpO2, Temperature, Hemoglobin), time of collection
- Complete lesion assessment, time of assessment
- Severity score: ISS, IGSII, revised trauma score, TRISS
- Possible hemostasis surgery, administration of tranexamic acid, type of surgery, time of day
- Blood products transfused: name of the components transfused, time of administration
- Transfused blood derivatives: fibrinogen, ..., time of administration
- Evolution of amine requirements, administered syringe flow rate, administration time
- Evolution of hemostasis parameters
- Respiratory evolution: ventilation parameters (duration of mechanical ventilation, FiO2, etc.), ARDS-type complications
- Length of stay in Intensive care unit, mortality, date and time of death
- Length of stay, in-hospital, and 30-day mortality.

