### **7.2 Investigator's responsibilities**

#### **7.2.1 Notification of AE to the sponsor**

The investigator should report all biological and clinical AEs in the CRF. and report them to the sponsor if necessary.

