#### **7.2.2 What should be declared?**

• **Expected SAEs:**

○ **subject to immediate notification by the investigator:**

- Allergic reactions
- TACO (transfusion-associated circulatory overload)

In sporadic cases, transfusion of fresh frozen plasma may result in allergic reactions or respiratory complications. Therefore, it is important to observe whether the same clinical events occur with FLYP even though the method of manufacturing freeze-dried plasma reduces this risk.

- **not requiring immediate notification by the investigator**

Serious adverse events related to the natural and usual course of the disease and not related to the investigational treatment, nor the acts and procedures added by the research:

- Aggravation of hemorrhagic shock
- Any complications secondary to hemorrhagic shock
- Hospitalization for any length of time: patients suffering from hemorrhagic shock in a traumatic context will benefit from multidisciplinary care in the hospital, including intensive care, surgery, medicine, and functional rehabilitation.
- Death: as the death rate for severe trauma patients is around 50%; given the high activity of the receiving departments, the coordinating investigator must be notified of death via [name] within 72 hours. The coordinating investigator will transmit the information to the promoter (Research and Innovation [REDACTED])

- **Unexpected SAEs:**

Upon **arrival at the hospital**, the patient will be taken care of by the hospital's emergency or intensive care unit, and a follow-up of the initial workup will be performed.

- After the extension workup, a prognosis can be given. Any unexpected worsening of the patient's existing condition that is not consistent with the prognosis given by the initial extension workup should be considered an SAE and reported by the hospital investigating physician.

- **The occurrence of in utero exposure**

Any pregnancy in which the fetus (from pre-embryonic stage to birth) may have been exposed at any time to FLYP, even if not associated with an adverse event, should be reported to the sponsor without delay.

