### 1734 **Secondary endpoints**

- 1735     ▪ Comparison of fibrinogen changes by group: paired t-test, analysis of covariance
- 1736     ▪ Comparison of the volumes of blood loss, volumes infused or transfused, the quantity of amines
- 1737     used between the two groups (Chi2, Fisher's exact, Student's, Mann-Whitney tests).
- 1738     ▪ Comparison of the INR differential, delta INR : [INR at hospital admission - initial INR at the
- 1739     point of injury] between the two groups

- 1740                   ▪ We will compare the Delta-INR values between the plasma and control groups using a
- 1741                   linear mixed model with an independent covariance matrix, considering study group, time, and
- 1742                   Injury Severity Score levels as fixed effects and incorporating a random intercept.
- 1743                   ▪ Comparison of the length of stay in intensive care between the 2 groups : Student's t test, Mann-
- 1744                   Whitney test.
- 1745                   ▪ Number of days of hospitalization: Student's t-test, Mann-Whitney test
- 1746                   ▪ Survival analysis over the first 30 days: Kaplan Meier graphic, log-rank test.
- 1747                   ▪ Feasibility endpoint : listing of technical and logistical difficulties in plasma administration ,
- 1748                   number ad percentage of patients, number and percentage of plasma vials.
- 1749                   ▪ The analysis will all take into account a possible center effect.
- 1750                   ▪ Safety Endpoint is the occurrence of any of the following adverse events: thrombosis, allergic
- 1751                   symptoms, transfusion-related acute lung injury, and transfusion-associated circulatory
- 1752                   overload. The traceability of plasma, including prescription, delivery, and follow-up
- 1753                   procedures, will be assessed using the plasma follow-up sheet from the French Military Blood
- 1754                   Institute. The Health Defence Service will realize the qualitative and quantitative analysis of
- 1755                   Adverse Events. There is no formal statistical test preplanned
- 1756                   ▪ If the initial characteristics of patients are unbalanced between the two groups after
- 1757                   randomization, an adjusted analysis will be considered with a regression method. Where

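### The SAP's four safety events and the protocol's reporting rules do not match, which risks incomplete and arm-dependent ascertainment in hospital

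*Combined protocol and SAP*

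**What the plan says.** SAP section 16.7, under the secondary endpoints, defines the outcome: "Safety Endpoint is the occurrence of any of the following adverse events: thrombosis, allergic" "symptoms, transfusion-related acute lung injury, and transfusion-associated circulatory" overload. That makes four components. SAP section 16.2 adds safety of prehospital plasma as an objective, and the SAP Harms section reports adverse events by arm.

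The protocol's rules for getting these events into the data are spread over several sections:

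- Section 7.2.1: "The investigator should report all biological and clinical AEs in the CRF".
- Section 7.2.2 lists, as expected SAEs "subject to immediate notification by the investigator", allergic reactions and TACO. A second class needs no immediate notification. It covers SAEs that belong to the usual course of the disease and are unrelated to the study treatment, and it includes "Any complications secondary to hemorrhagic shock".
- Section 7.2.3 requires any SAE up to day 30 or death to be reported within 24 hours.
- Section 7.4, prehospital phase: the treating physician reports adverse events and their aggravation.
- Section 7.4, on admission: "The occurrence of an unexpected event or worsening of an unexpected event in the hospital phase will be reported" by the department in charge.
- Section 3.9, hospital data list: "ARDS-type complications" appears under respiratory evolution. There is no thrombosis item.

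The reporting flowcharts in section 7.6 and the CRF itself are not in the material available.

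**The concern.** The SAP counts four named events, but a hospital site working from section 7 finds only two of them. It also meets a hospital-phase instruction that differs from the rule that applied minutes earlier in the ambulance. Lung injury, overload and thrombosis would be expected to surface mainly after admission, where the narrower wording applies.

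The trial is open-label (section 3.8). If recording an event depends on a site first deciding whether it belongs to the injury or to the plasma, that decision is made with the arm known. A difference or a similarity between arms in the safety endpoint could then partly reflect how events were looked for and classified. Section 8.1 of the protocol plans a test of adverse-event incidence, while SAP section 16.7 and the Harms section plan none. That is a separate inconsistency, but either way the two arms' counts will be set side by side.

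**Working it through.** The plan gives no assumed rate, precision or power for the safety endpoint, so there is no figure of its own to reproduce. The check is a cross-reading, followed by a labelled illustration.

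**Step 1. Match the four components to the protocol text.**

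| SAP component | Named for immediate notification (7.2.2) | Called expected (7.2.2) | Caught by the 7.4 hospital sentence, read literally | Own item in the 3.9 hospital list |
|---|---|---|---|---|
| Allergic symptoms | yes | yes | no | no |
| TACO | yes | yes | no | no |
| TRALI | no | no | depends on the test used | partly (ARDS-type complications) |
| Thrombosis | no | no | depends on the test used | no |

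Unnamed in section 7: 2 of 4 = 50% of component names. This is not a share of events. Section 7.2.2 does mention respiratory complications of plasma in an explanatory sentence, but not TRALI.

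**Step 2. Which events are unexpected?** Section 7.1.1 judges an unexpected serious event against the Investigator's Brochure or product information. Section 7.2.2 judges it, in hospital, against the prognosis after the initial workup. Under the first test, TRALI and thrombosis may count as unexpected. Under the second, either could fit the prognosis of a severely injured patient and so not count. Section 7.4 does not say which test applies.

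**Step 3. Notification of serious events.** Section 7.2.3 says any SAE within 24 hours; section 7.2.2 removes disease-course SAEs from immediate notification. A site must therefore decide on relatedness before it knows which rule applies. The independent committee rules on the causality of events that investigators report, and is informed of those related to FLYP (section 7.5). An event that a site attributes to shock may not reach it. Section 7.2.3 also covers serious events only, whereas the SAP endpoint sets no severity threshold.

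**Step 4. Is ascertainment the same in both arms?** FLYP comes with a clinical and biological monitoring form (section 5.1.2), which is returned to the CTSA (section 5.1.8). SAP section 16.7 uses the plasma follow-up sheet. No equivalent form is described for saline in section 5.2. FLYP patients thus have one more route by which an event may be noted.

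**Step 5. Illustration only; the capture rates and the event rate are assumptions.** With n = 70 per arm (protocol Summary) and no recorded events, the one-sided 95% upper bound is 1 − 0.05^(1/70) = 4.2%. If a fraction s of events is recorded, the bound on the true rate is 4.19%/s:

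- s = 100%: 4.2%
- s = 75%: 5.6%
- s = 50%: 8.4%
- s = 25%: 16.8%

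For unequal capture, assume a true rate of 5% in both arms. Full capture in one arm gives 70 × 0.05 = 3.5 expected records, and half capture in the other gives 70 × 0.05 × 0.5 = 1.75. That is an apparent ratio of 2 with no true difference. Nothing in the documents says that capture is this low, or which arm would be favoured.

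**The case against.** The strongest reply is that every one of these events already has a route into the data. Section 7.2.1 asks for all adverse events in the CRF. Section 3.3.2 has the hospital investigator follow AEs and SAEs for 30 days. The schedule in section 3.3.5 marks adverse events in every phase. Section 7.2.3 covers any SAE, and section 7.2.4 adds hemovigilance declaration without delay. The SAP counts adverse events, not expedited reports, so slow notification would not in itself lower the count. Treatment and transfusion times are collected (section 3.9) and SAE reports carry the date of occurrence (section 7.2.4), so timing can often be reconstructed.

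This stands, and it rules out three stronger readings that a reader might infer:

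- That TRALI and thrombosis need not be notified. A serious case falls under section 7.2.3, and the shock-complication exemption applies only to events unrelated to treatment. A lung injury judged transfusion-related is outside it.
- That hospitals report unexpected events and nothing else. Section 7.4 does not say so and does not cancel sections 3.3.2, 7.2.1 or 7.2.3.
- That the endpoint will be undercounted. The documents give neither an event rate nor a capture rate.

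The reply does not remove the conflict itself. A general duty to record everything sits beside a narrower hospital instruction and an exemption that needs a causality judgment. The hospital data list gives thrombosis no prompt. The section 7.6 figures or the CRF might supply one; that cannot be checked here.

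**Conclusion.** The mismatch is real. Two of the four SAP safety components are not named in the text of section 7. The hospital-phase sentence in section 7.4 conflicts with section 7.2.1 and with the prehospital rule. Section 7.2.2 and section 7.2.3 give different instructions for serious events attributed to shock. The consequence is a risk of incomplete and arm-dependent ascertainment in an open-label trial. Its size and direction cannot be computed from the documents: the extra FLYP form could raise counts in that arm, while unblinded attribution could move them either way. The percentages in the illustration rest wholly on assumed capture and should not be cited as an estimate of undercounting. The conclusion assumes that the section 7.6 flowcharts and the CRF do not already list the four components; if they do, only the wording conflicts remain.

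**What to change.** 1. In section 7.4, hospital phase, replace *unexpected event* with *adverse event*, so that it agrees with section 7.2.1 and the prehospital rule.
2. In the hospital CRF, record each of the four SAP components (yes/no, onset date and time) in both arms through day 30, whatever the site's view of causality.
3. Reconcile the event list and the shock-complication exemption in section 7.2.2 with section 7.2.3 and with the SAP endpoint, so that a site can tell which rule governs a lung injury or a thrombosis.

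The cost is a wording change in two sections, a few CRF lines and slightly more adverse-event recording. Expedited notification of every new ARDS is not needed for this purpose. It would add reporting load in severely injured patients, and uniform CRF recording already addresses the count that the SAP uses.

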## 7.5 Data Safety Monitoring Board (DSMB/ CSI)

An oversight committee made up of members independent of the project will be set up:

Department of anesthesia and intensive care

Hematology-Transfusion Unit

This committee is informed during the study of any AE/SAE related to the administration of FLYP.

He is informed, in writing, by the promoter, and the information relating to the follow-up of the AEs will be transmitted to him.

It will be responsible for ruling on the causality of AEs reported by investigators during the trial. It has an advisory function when called upon by the sponsor on medical issues such as tolerance and adverse events.

The committee will decide whether or not to stop the study and whether or not to discharge the patient from the study. The recommendations concerning the continuation, possible modifications, or premature termination of the study will be transmitted to the sponsor.

This committee meets once every six months, except in particular cases.

## 7.6 Reporting of Adverse Events

[figure not shown]

1104  
1105  
1106

[figure not shown]

## 8 STATISTICS

### 8.1 Analysis plan

The complete statistical analysis plan is the subject of a separate document.

We will report categorical variables as frequencies (%) and use Fisher's exact test to compare. Continuous variables will be expressed as medians (IQR) and will be compared using the Mann-Whitney U test. The effect sizes will be represented by the median difference (95% CI) for continuous variables and the risk ratio (95% CI) for categorical variables. All comparisons will use two-sided tests, and a P value of less than 0.05 will be considered to indicate statistical significance. We will not use any correction to account for multiple comparisons.

#### **A comparison of key patient characteristics will be performed to validate the comparability of the two groups.**

This comparison will be made for the main variables of interest :

Age, sex, comorbidities, type of injury, mechanism of injury, anatomic localisation of trauma, time response of advanced life support teams, vital status at the point of injury (blood pressure, heart rate, shock-index, oxygen saturation), prehospital biological measures (Prothrombin time and INR value, Hemoglobin and lactic acid concentrations), body temperature, basic life support therapeutics, advanced life support therapeutics, cumulated crystalloid volume, cumulated plasma volume, prehospital red cell units transfused, vital signs on arrival at the intensive care unit (blood pressure, heart rate, shock-index, injury severity score, traumatic brain injury confirmed with CT scan, laboratory values - Hemoglobin, platelets, lactic acid, base excess)

The analysis will take into account a possible center effect

### **Data Analysis for Primary Endpoint:**

- For the primary outcome analysis, INR at hospital admission will be considered to have been performed at a comparable time in each patient and will be compared across the two arms with the Mann–Whitney U test. If the initial characteristics of patients are unbalanced between the two groups after randomization, an adjusted analysis will be considered with a regression method.
- When appropriate, both adjusted and unadjusted results will be reported.

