# **3 DESIGN**

## **3.1 Outcome variables**

### **Primary endpoint:**

- The primary endpoint is the international normalized ratio (INR) at hospital arrival.

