### **3.3.1 Prehospital phase**

This phase is performed by a prehospital investigator after verification of inclusion and non-inclusion criteria. During this phase, no fibrinogen or other coagulation factors, other than FLYP

Before the administration of the experimental treatment, the management of a patient will be :

- Stop the bleeding (tourniquet or hemostatic dressing or pressure point if necessary)
  - Measure clinical and biological parameters (HR, BP, SpO2, hemoglobin level,...)
  - Take a sample (1 drop of blood) to measure the prehospital PT/INR with the Coaguchek®.
  - If possible, take a venous sample before any drug administration, using two blue tubes (PT, aPTT, fibrinogen, coagulation factors) and two purple tubes (blood group, platelets, etc.).
- Particular attention must be applied to the filling of the tubes, which must be COMPLETE so that the results of the analyses can be interpreted.

- Ventilatory support with oxygen supply (high concentration mask or orotracheal intubation and mechanical ventilation)
- **For the FLYP (+) group: Administration of FLYP, up to 4 units (800ml)**  
Plasma units are reconstituted as needed.  
Any connected and opened bottles are left with the patient.
- **For the FLYP (-) group: Administration of saline solution,** as much as necessary to reach the goals recommended by the guidelines.

Then, for the two groups, according to the patient's clinical parameters:

- Use of amines, and tranexamic acid
- The dosage of crystalloids and the use of amines should make it possible to reach the goals recommended by the guidelines.

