#### **5.5 Practical procedures for accounting, storage, and delivery of experimental treatments within the investigating centers**

The experimental treatments are packaged and supplied by the CTSA. They will be distributed in batches of 2 (1 FLYP and one normal saline), either by the CTSA for the BSPP or by the regional Etablissement Français du Sang-EFS (tripartite agreement between the CTSA, the regional EFS, and the recruiting center) for the other prehospital investigating centers.

Study treatments will be stored and accounted for at each center. A copy of the detailed delivery note (date of shipment, lot number, quantity, expiry date) of the CTSA shipments will be kept there (Appendix 2). In these centers, these treatments will be stored in the in-house pharmacies under the same conditions as the other treatments routinely used in the prehospital setting but in a space specifically dedicated to the study.

Only one experimental treatment (bag containing FLYP or not) will be made available to the prehospital team in the AR or in the SMUR.

This treatment will be taken out of its packaging only when it is used.

As soon as the physician comes back from the intervention, he must return all the study elements to the center's manager.

No vial of FLYP from an opened batch shall be present in any AR/SMUR.

Unused, expired or unused FLYP units will be redirected to the CTSA.

Any FLYP that has not expired but is not usable due to improper storage conditions or any other reason must also be returned to the CTSA (with details of nonconformities) for inspection.

Suppose the FLYP is destroyed by the user (degradation without the possibility of a return to the CTSA) or in case of loss. In that case, the delivery slip will be returned to the CTSA with the mention destruction or loss of product at the level of the batch number, a duplicate will be kept at the concerned recruiting center.

Used and empty bottles will be thrown away (Incineration of hospital waste - DASRI).

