- 1685                   ● Recruitment, Withdrawal and Follow-up
- 1686                             ▪ The "CONSORT" diagram will report the number of people screened, eligible, consented,
- 1687                             randomized, receiving their allocated treatment.
- 1688                             ▪ The level of consent withdrawal will be tabulated as consent to continue follow-up and data
- 1689                             collection
- 1690                             ▪ Timing and number of patients lost to follow-up will be presented in a Kaplan-Meier Diagram.
- 1691                             ▪ The numbers of losses to follow-up will be summarized per treatment arm
- 1692                   ● Baseline patient characteristics
- 1693                             ▪ Patients will be described with respect to age, sex, comorbidities, type of injury, mechanism of
- 1694                             injury, anatomic localization of trauma, time response of advanced life support teams, vital
- 1695                             status at the point of injury (blood pressure, heart rate, shock-index, oxygen saturation),
- 1696
- 1697

1698 prehospital biological measures (Prothrombin time and INR value, hemoglobin and lactic acid  
1699 concentrations), body temperature, basic life support therapeutics, advanced life support  
1700 therapeutics, cumulated crystalloid volume, cumulated plasma volume, prehospital red cell  
1701 units transfused, vital signs on arrival at the intensive care unit (blood pressure, heart rate,  
1702 shock-index, injury severity score, traumatic brain injury confirmed with CT scan, laboratory  
1703 values - hemoglobin, platelets, lactic acid, base excess)

1704

- 1705     ▪ The description will be reported separately for the two randomized groups. Categorical data will
- 1706     be summarized by numbers and percentages. Continuous data will be summarized by mean, SD,
- 1707     and range if data are Gaussian, and median, IQR, and range if data are skewed. Tests of
- 1708     statistical significance will not be undertaken for baseline. Instead, the clinical importance of
- 1709     any imbalance will be noted.

1710

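### The primary comparison has no assured use of prehospital INR or centre, adjusts only if imbalance is noticed, and does not confine adjusters to pre-treatment variables

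*Combined protocol and SAP*

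**What the plan says.** **Endpoint and test.** Protocol section 3.1: "The primary endpoint is the international normalized ratio (INR) at hospital arrival". Under Data Analysis for Primary Endpoint in section 8.1, the arrival measurement is treated as having been "performed at a comparable time in each patient and will be compared across the two arms with the Mann–Whitney U test". SAP section 16.7 (First endpoint) says the same.

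**Adjustment.** The rule is one sentence: "If the initial characteristics of patients are unbalanced between the two groups after randomization, an adjusted analysis will be considered with a regression method". On reporting: "When appropriate, both adjusted and unadjusted results will be reported". Neither document names the covariates, the form of the regression, what counts as unbalanced, or which result is the primary one. SAP section 16.6 adds that baseline variables will not be significance-tested and that the clinical importance of any imbalance will be noted.

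**Prehospital INR.** Section 3.3.1 has the team take a drop of blood before the experimental treatment "to measure the prehospital PT/INR with the Coaguchek". This value then appears in the comparability list and in the secondary delta-INR analysis.

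**Centre.** Section 8.1 closes its comparability paragraph by saying that a possible centre effect will be taken into account, and SAP section 16.7 repeats this under its secondary endpoints. Boxes are randomised in blocks of two (section 3.2.2) and supplied to centres in pairs, one of each arm (section 5.5).

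**The list of characteristics.** The section 8.1 list used to judge comparability includes "cumulated crystalloid volume, cumulated plasma volume, prehospital red cell units transfused, vital signs on arrival at the intensive care unit". SAP section 16.6 gives the same variables under the heading Baseline patient characteristics, including "therapeutics, cumulated crystalloid volume, cumulated plasma volume, prehospital red cell" units.

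**The concern.** A coagulation value taken before treatment is the natural predictor of the same measurement at arrival. Using it costs nothing in patients, and SAP section 16.5 says the number of patients could not be increased. As written, it enters the primary comparison only if someone judges it unbalanced and then decides to adjust.

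Centre is similar. Section 8.1 names hospital clustering for delta-INR and centre stratification for transfusion requirement, but no technique for the primary endpoint. A plain Mann–Whitney test cannot take centre into account.

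Two further things are at stake. With no threshold, covariate set or leading result fixed, the headline answer in an open-label trial could depend on choices made after the data are seen. And the only list of patient characteristics in the documents mixes pre-treatment variables with the treatment itself (plasma volume) and its possible consequences (ICU-arrival vital signs and laboratory values). Plasma volume will differ between arms by design. If such variables were used as adjusters, the model would no longer estimate the effect of assignment to plasma.

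**Working it through.** **1. Reproduce the plan's own figure.** Inputs from protocol section 8.2 and SAP section 16.5: difference 0.3, SD 0.4, two-sided alpha 0.05, power 80%.

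n per group = 2 × [0.4 × (1.960 + 0.842) / 0.3]² = 27.9, so 28. The t-test version gives 29. Dividing 28.9 by the Mann–Whitney efficiency of 0.955 gives 30.3. The stated 30 coagulopathic patients per group is reproduced. At 50% incidence that is 60 per group; with a 10% loss, 60 / 0.9 = 67, which the plan rounds to 70. The sample size is not in error. It is sized for an unadjusted comparison.

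**2. Precision available from the prehospital INR.** The correlation ρ between prehospital and arrival INR is in neither document, so a range is shown. The plan sizes 0.3 for coagulopathic patients but analyses everyone in the modified intention-to-treat population. *Assumption:* the effect is 0.3 in the coagulopathic half and nil in the rest, so the mean difference is 0.5 × 0.3 = 0.15, with the SD still 0.4 and 60 per arm.

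Residual SD = 0.4 × √(1 − ρ²); SE = residual SD × √(2/60); power = Φ(0.15/SE − 1.96).

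| ρ (assumed) | Residual SD | SE | 0.15/SE | Power |
|---|---|---|---|---|
| 0 (same as unadjusted) | 0.400 | 0.0730 | 2.05 | 54% |
| 0.3 | 0.382 | 0.0697 | 2.15 | 58% |
| 0.5 | 0.346 | 0.0632 | 2.37 | 66% |
| 0.7 | 0.286 | 0.0522 | 2.88 | 82% |

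If the 0.3 effect applied to all 60 per arm, unadjusted power would already be Φ(0.3/0.0730 − 1.96), about 98%. The power argument therefore rests on the dilution assumption.

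**3. What the imbalance trigger recovers.** Simulation with normal data, 60 per arm and 6,000 trials per setting. The plan gives no threshold, so for illustration the trigger is a 5% t-test on prehospital INR. Monte Carlo error for power is at most √(0.25/6000), about 0.65 points; for the type I error rates it is about 0.3 points.

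| | ρ = 0.3 | ρ = 0.5 | ρ = 0.7 |
|---|---|---|---|
| Power, Mann–Whitney | 52% | 51% | 51% |
| Power, always adjusted | 57% | 65% | 82% |
| Power, adjusted only if triggered | 52% | 52% | 52% |
| Type I error, adjusted only if triggered | 4.5% | 4.3% | 3.2% |
| Type I error, better of the two results | 6.5% | 7.4% | 7.7% |

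The trigger recovers almost none of the gain. Followed mechanically, it does not inflate type I error. Free choice of the more favourable result does.

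**4. Why post-randomisation adjusters matter.** Illustration only: 60 per arm, one to four units in the FLYP arm and none in control, and an effect proportional to volume averaging −0.30. Adding plasma volume to the model moves the arm coefficient from −0.30 to about 0.00 and power from about 98% to about 5%. This follows from the set-up, since an effect exactly proportional to volume leaves nothing for arm. It shows the mechanism and does not forecast what this trial's analysis would do.

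**The case against.** **The named test is valid.** Randomisation protects an unadjusted Mann–Whitney comparison. The adjusted analysis is an addition, with both results to be reported where appropriate. This stands: a reader might infer that the primary result is biased, and the documents do not support that.

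**Centre is not ignored.** A reader might infer from the primary-endpoint paragraph that centre was overlooked. The sentence just before it in section 8.1, and another in SAP section 16.7, promise to take it into account. What remains is that no method is given for the primary endpoint. Paired supply should help balance arms within centre, though returned or expired boxes make this approximate.

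**The rule does not direct adjustment for plasma volume.** A reader might infer this because that volume is on the list and must differ between arms. But the rule speaks of initial characteristics and cites no list, SAP section 16.6 describes a descriptive table, and the plasma-to-crystalloid ratio has its own explanatory model (section 8.1, SAP section 16.9). What stands is that the list is mislabelled and nothing excludes its post-randomisation entries.

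**Prehospital INR is not lost.** It is on the comparability list and feeds the secondary delta-INR analysis. That is correct, but neither gives it an assured place in the primary comparison.

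**The gain is uncertain and has a cost.** The correlation is unknown, and at 0.3 the gain is only about 4 points. The prehospital point-of-care test was added by amendment in 2017, so some earlier values may be missing. A log-scale model would also replace the planned median difference. These are fair points about size and cost; they do not supply the missing specification.

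**Conclusion.** The point holds as one of incomplete specification and forgone precision, not invalidity. The primary comparison makes no assured use of a pre-treatment INR already collected and gives no method for centre. It leaves adjustment, covariates and the leading result to judgement after the data are seen.

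The gain depends on a correlation that the documents do not give. Under the assumed mean difference of 0.15, SD 0.4 and 60 per arm, it runs from nothing at a correlation of 0 to about 28 percentage points at 0.7 (54% to 82%). These are raw-scale, normal-theory figures. If the full 0.3 effect applied to every patient, power would not be a concern, so the documents do not support a flat statement that the trial is underpowered.

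The cost of discretion is a type I error of about 6.5% to 7.7% in the settings simulated, and only if the better of two results may be chosen. Bias would arise only if post-randomisation variables were used as adjusters, which the plan neither announces nor rules out.

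**What to change.** - Pre-specify one regression of arrival INR (log scale if skewed) on arm, prehospital INR and centre, with small centres pooled, to be fitted whatever imbalance is seen.
- State whether this model or the Mann–Whitney test leads. If the Mann–Whitney test is kept, stratify it by centre.
- Delete the imbalance trigger from protocol section 8.1 and SAP section 16.7.
- Limit adjusters in any model of treatment effect to variables measured before study treatment.
- Move plasma and crystalloid volumes, prehospital red cells and ICU-arrival values out of the SAP section 16.6 baseline list into a separate post-randomisation table. Make the matching change to the section 8.1 list.

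No extra patients or measurements are needed; the change is to the analysis wording. There are two small costs. Missing prehospital INR values must be handled by the multiple imputation already planned (section 8.5, SAP section 16.8), so the number missing should be reported. A log-scale model gives a ratio, so the planned median difference would need to be shown beside it.
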